#### Statistical analyses

Descriptive and comparative analyses will be performed separately for each type of tumor: CRC (Group A), GEC (Group B), and PC (Group C) as well as at a pan-tumor level, comparing all EOGIC to non-EOGIC patients.

Population characteristics will be described using measures of central tendency and dispersion for continuous variables and frequencies and percentages for categorical variables. Normality of the sample will be analyzed for continuous variables through histogram exploration, the Shapiro–Wilk test, and homoscedasticity by Levene's test. Group comparisons will be made using Student's t-test or Mann–Whitney U test for continuous variables and Pearson's Chi-square test or Fisher's exact test for categorical variables. Correlation between different measurements and conditions of interest will be assessed using Pearson's or Spearman's correlation tests.

Analyses for circulating inflammatory proteins, the microbiota and the tumor microenvironment proteome, will be conducted utilizing specialized software for each application. Raw data will be processed, applying quality criteria, and differential signatures between groups will be identified. For signature identification, previously mentioned tests, including correction methods for multiple comparisons such as the false discovery rate (FDR).

For pan-tumor and gender/sex-level comparisons, machine learning algorithms will be used, allowing integration of all patient clinical and lifestyle profile data with variables derived from circulating inflammatory proteins, microbiome and tumor microenvironment proteome profiles, identifying clusters of patients with similar patterns.

Statistical analysis will be performed using IBM Statistical Package for the Social Sciences (SPSS) version 24.0, GraphPad Prism v9, and R 4.1.0 (R Foundation for Statistical Computing, Vienna, Austria. http://www.R-project.org/).

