Some studies have assessed differential clinical and molecular characteristics of EOGIC, proposing the recognition of a novel entity with special requirements for diagnosis and clinical management. EOGIC usually presents in advanced clinical stages and with aggressive phenotypes, including poor differentiation, signet ring histology and vascular-perineural invasion [17]. EOCRC typically occurs in the distal colon and rectum, with a higher proportion of microsatellite unstable tumors, fewer cases of mutations in *APC*, *KRAS*, and *BRAF*^V600E^, and mostly with a molecular subtype related to infiltration of inmune cells [18–20]. Interestingly, it has been linked to a distinctive microbiota [21]. EOGEC commonly associates with atrophic gastritis from autoinmune phenomenons. It presents higher tumor grades, higher proportion of poorly cohesive histology and signet-ring cell subtype, with an increment of CDH1 mutations, as well as the molecular subtype EBV (TCGA classification) [20, 22]. Early onset pancreatic cancer has lower proportion of *KRAS*, while *SMAD4* mutations are more frequent. Different signaling pathways like Hedgehod, TGFβ, hypoxia or PI3K/AKT have also been reported in these patients [23, 24].

Additionally, EOGIC patients have distinctive characteristics that affect their clinical management. Due to their extended life expectancy, they face long-term effects from therapeutic strategies, which may impact their quality of life and more specifically their sexual and reproductive health. Furthermore, cancer diagnosis at a young age normally represents a more pronounced psychological disorder derived from its impact on professional, social and familiar commitments. This is why it is essential to treat these patients individually, considering all these factors and providing a more personalized and precise approach [6, 25–30].

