#### Histopathological data and tissue proteome

General histopathological and molecular characteristics of the tumor will be comprehensively studied, via specific determinations relevant for each of the etiologies.

General histopathological characteristics, tumor location and clinical tumor stage will be recorded. Colorectal and gastroesophageal cancer staging will be assessed according to The Eighth Edition AJCC Cancer Staging Manual [39]. Pancreatic cancer will be classified as resectable, borderline resectable, locally advanced unresectable and metastasic. Number of metastasic sites and their location will also be recorded in stage IV of the disease. Histology type and differentiation grade will be assessed in formalin-fixed paraffin-embedded (FFPE) tissue. Molecular characteristics to be recorded in FFPE tissue include MMR/MSI status by immunohistochemical analysis of mismatch-repair proteins (*MLH1, MSH2, MSH6*, and *PMS2*) as well as CD3 and CD8 infiltration in all tumors. Additional molecular characteristics will also be measured according to tumor type: *HER2* amplification status, *KRAS*, *NRAS* and *BRAF* mutations for CRC; *HER2* overexpression/amplification status, PDL1 (CPS) and CLDN 18.2 and FGFR2b expression for GEC; and *KRAS* mutations for PC. For all tumors, Next-Generation Sequencing (NGS) analyses targeting cancer-related genes will be performed if a suitable sample is available.

Histopathological characteristics will be preferentially assessed in the recruitment center. If available after routine determinations for diagnosis and clinical management, FFPE tissue samples will be sent to the Pathology Department of HUN in order to perform a centralized assessment of missing determinations.

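### The colorectal comparison uses only unadjusted two-group tests, although the protocol expects early-onset tumours to be more often distal or rectal, so a marker that follows tumour location can be read as an early-onset signature

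*Protocol article*

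**What the plan says.** The Statistical analyses section sets the units of comparison: "Descriptive and comparative analyses will be performed separately for each type of tumor: CRC (Group A), GEC (Group B), and PC (Group C"), plus a pan-tumor comparison. It then names the tests: "Group comparisons will be made using Student's t-test or Mann–Whitney U test for continuous variables and Pearson's Chi-square test or Fisher's exact test", the last two being meant for categorical data. The circulating proteins, microbiota and tissue proteome get the same tests: "For signature identification, previously mentioned tests, including correction methods for multiple comparisons such as the false discovery rate (FDR"). No model, stratum or covariate is named for any of these comparisons.

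The Background describes how case mix differs by age at onset. In colorectal cancer, "EOCRC typically occurs in the distal colon and rectum, with a higher proportion of microsatellite unstable tumors". In early-onset gastroesophageal cancer it reports a "higher proportion of poorly cohesive histology and signet-ring cell subtype".

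Both variables are collected. Under Histopathological data and tissue proteome: "General histopathological characteristics, tumor location and clinical tumor stage will be recorded", and "Histology type and differentiation grade will be assessed in formalin-fixed paraffin-embedded (FFPE) tissue".

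**The concern.** Within group A, colorectal tumours from all locations are compared as one block. If EOGIC patients have more distal and rectal tumours, any marker whose level depends on location will differ between the age groups, even if early-onset and later-onset tumours at the same location are identical. The named tests cannot tell these two explanations apart. FDR limits false discoveries from testing many markers; it does nothing about a difference produced by case mix.

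This matters because the study wants more than a description of where tumours sit. The Discussion aims at unique biomarkers and new therapeutic targets, and the Background argues that EOGIC is a distinct entity. A tissue-proteome, microbiome or CD3/CD8 difference that exists only because more of the young patients have rectal tumours would serve neither purpose. The problem acts inside the tumour-specific analysis, so separating the three tumour types does not remove it.

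**Working it through.** **The plan's own figure.** The Patient selection and recruitment section gives a detectable Cohen's d of 0.385 at 80% power and 5% significance. For 80 v 160 patients, two-sided, the t-based value is 0.3852, so the figure reproduces. It belongs to the pan-tumor comparison and this point does not affect it.

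**Inputs from the documents.** 40 EOGIC and 80 non-EOGIC colorectal patients; 5% significance; 80% power.

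**Inputs assumed, because the documents give none.** Distal or rectal share q1 = 80% in EOGIC and q0 = 50%, 60% or 65% in non-EOGIC. A marker with SD 1 within location and a difference D = 0.5, 1 or 2 SD between locations. No age effect within location.

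**Crude test.**
- Shift between group means: D × (q1 − q0).
- Variance in each group: 1 + D² × q × (1 − q).
- Pooled variance v: the two variances weighted 40:80.
- SE = √[v × (1/40 + 1/80)].
- Rejection rate: Φ(−1.96 + shift/SE) + Φ(−1.96 − shift/SE).

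Example, 80% v 60% and D = 1:
- Shift = 1 × 0.20 = 0.20.
- Variances: 1 + 0.16 = 1.16 and 1 + 0.24 = 1.24.
- v = (40 × 1.16 + 80 × 1.24)/120 = 1.213.
- SE = √(1.213 × 0.0375) = 0.213, and shift/SE = 0.938.
- Rejection = Φ(−1.022) + Φ(−2.898) = 0.153 + 0.002 = 0.155.

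All nine cases:

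| Distal/rectal share, EOGIC v non-EOGIC | D = 0.5 | D = 1 | D = 2 |
|---|---|---|---|
| 80% v 65% | 7% | 11% | 21% |
| 80% v 60% | 8% | 16% | 33% |
| 80% v 50% | 12% | 29% | 62% |

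Simulating the t test directly (4,000 runs per case) gives 7-11% at 0.5 SD and 11-62% at 1-2 SD. With location added to a linear model, the rate is about 4.4-5.5%. A second set of assumptions (80% v 65%, 80% v 60% and 85% v 55%; D from 0.5 to 1.5) gives 7-51% for the crude test.

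**Cost of adjusting.** The detectable d is 2.80/√W, where W sums n1 × n0/(n1 + n0) over location strata.
- Unadjusted: W = 40 × 80/120 = 26.67, so d = 0.543.
- 80% v 60%: strata of 32 v 48 and 8 v 32, so W = 19.2 + 6.4 = 25.6 and d = 0.554.
- 80% v 65%: d = 0.549. 80% v 50%: d = 0.567. 85% v 55%: d = 0.568.

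**Gastroesophageal group, 20 v 40.** The same arithmetic applies to any two-category mix. With the shares above and D of 1-2 SD, the simulated crude rate is about 8-34%. The protocol gives no histology shares, so this shows only what a mix difference can do. Adjustment would move the detectable d from 0.767 to about 0.78-0.80.

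**The case against.** The strongest reply is that the aim is descriptive. The study sets out to characterise EOGIC, and the total difference between the age groups is a legitimate target. In the calculation above the group means really do differ, by 0.075 to 0.6 SD, so the crude test is detecting a true marginal difference. This stands. A reader might take the 7-62% as an inflated type I error of the planned test. It is an error rate only for the claim that the difference holds within location, and no section of the article states that estimand.

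A reader might go further and infer that a feature should count as distinctive of EOGIC only if it persists within location. The documents do not support such a gate. On the Background's own account, distal location may be part of the early-onset phenotype, and conditioning on it could remove some of what the study wants to describe.

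A reader might also extend the location argument to gastroesophageal cancer, as oesophagus or junction against stomach. The Background does not describe such a shift. What it reports that is relevant here is a difference in histology type.

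Location and histology are not unused. They fall under the descriptive tables and categorical group tests, and the machine-learning step integrates all clinical data. But that step is stated for pan-tumor and sex-level comparisons and looks for clusters; it does not adjust the comparison within colorectal cancer.

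Finally, an article may leave covariates to a fuller plan. That is fair for detail, but this article names specific tests and assigns those same tests to signature identification. The point concerns the stated method.

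**Conclusion.** The point holds for colorectal cancer. The stated tests cannot separate an early-onset difference from a location difference, the protocol itself expects the location imbalance, and the variable needed to separate them is collected. The crude comparison is valid as a description; it misleads only if a signature is presented as independent of location.

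The size is uncertain. Rejection of about 7-62% for a location-dependent marker rests wholly on the assumed shares and effects. The low end is close to nominal, and the top needs a 30-point gap in shares together with a 2 SD location effect. Markers that do not vary by location are unaffected. For gastroesophageal cancer only the histology version is supported, and as a supplementary analysis. No sample-size figure is wrong on this point. The change should be made, since it improves interpretation at little cost.

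**What to change.** Add the following to the Statistical analyses section.

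- **Colorectal cancer.** Beside each crude EOGIC v non-EOGIC comparison, report one adjusted for or stratified by recorded tumour location. Use a linear or logistic model with group and location, or a stratified rank or Mantel-Haenszel test. For omics, fit the same model to each feature and apply FDR to the group effects.
- **Location categories.** Fix them before analysis and keep them coarse. At an 80% distal or rectal share, only 8 of the 40 EOGIC patients would fall outside that stratum.
- **Labelling.** State for each reported signature whether it is a total or a location-adjusted difference. Location itself remains a described characteristic, and persistence within location is not a condition for reporting a feature.
- **Gastroesophageal cancer.** Base any supplementary adjusted result on recorded histology type, shown beside the crude result because histology may be part of the phenotype.

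The cost is wording, one or two degrees of freedom per model, and a detectable d in colorectal cancer of about 0.55-0.57 in place of 0.54. No further patients, samples or assays are needed.

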**Methods:**

Patients with histologically confirmed new diagnosis of colorectal, gastroesophageal and pancreatic adenocarcinoma will be considered for two cohorts: EOGIC (≤ 50 years old) and non-EOGIC (60–75 years old), with a ratio of 1:2. Two hundred and forty patients will be recruited in 4 Public Hospitals from northern Spain. After receiving unified informed consent, demographic and clinical data of the patients will be collected in a REDCap database. Lifestyle related data will be obtained in questionnaires assessing diet, physical activity and the general quality of life of the patients before diagnosis. Biological samples prior to any onco-specific treatment will be obtained for the analyses of circulating inflammatory proteins, gut microbiota, and the proteome of the tumor microenvironment. Histologic characteristics and routine biomarkers will be also collected. Thereafter, data will be integrated and analyzed to assess tumor specific, pan-tumor and sex-associated differential characteristics of EOGIC.

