### Patient selection and recruitment

Patients will be selected and recruited in routine medical appointments by specialized medical oncologists at the participating Hospitals during the period of 01/2024–12/2025. Patients will be included consecutively based on inclusion and exclusion criteria, following a ratio of 1 EOGIC: 2 non-EOGIC.

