#### Exclusion criteria

Eastern Cooperative Oncology Group (ECOG) performance status of ≥ 3.Presence of comorbidities which may compromise participation of the patient in the study (mainly in terms of capability to complete the questionnaires).Having received oncological treatment directed at the newly diagnosed cancer (i.e., at the time of inclusion the patient has not yet started any type of treatment, including surgery).

Although there is a lack of consensus in the age threshold to define EOGIC, it is generally set at 50 years old, in agreement with the initiation of most of the screening programs [6]. Regarding the non-EOGIC group, we set the lower age at 60 years old, in order to ensure a clear differentiation between groups; while the upper limit is established at 75 years old in order to exclude the very elderly population. Again, although the lack of consensus in the age to define elderly patients, several studies in the field consider 75 years old as the lower limit to define this population, and present evidence on their differential characteristics compared to on-average patients [32–36]. Age range is also defined with the objective to minimize age related confounding effect.

We estimate the following number of patients to be included in each group: CRC-group A, 40 EOGIC and 80 non-EOGIC; GEC- group B, 20 EOGIC, 40 non-EOGIC; PC-group C, 20 EOGIC, 40 non-EOGIC (Fig. 1a). Estimated number of patients has been calculated based on incidence of EOGIC in HUN in the years 2019–2022 (Fig. 1b), and assuming a similar incidence in the other participating hospitals, taking into account that all participating Hospitals cover a similar target population. The rate of patient inclusion will be evaluated periodically and if necessary, recruitment period will be extended or additional Hospitals of the geographical area will be invited to participate in the study in order to increase patient recruitment.

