**Fig. 1 Fig1:**
[figure not shown]
Estimated patient recruitment. **a** Diagram of the recruiting centers and estimated number of patients to be recruited by group. **b** Number of cases with GI cancer treated in Medical Oncology Unit of the HUN in the years 2019–2022. Red depicts EOGIC, while green depicts non-EOGIC (age > 50 years) CRC: colorectal cancer; EOGIC: early onset gastrointestinal cancer. GEC: gastroesophageal cancer; PC: pancreatic cancer

As aforementioned, patients will be included in a ratio of 1 EOGIC: 2 non-EOGIC with the aim of increasing sample-size in the control group, thus optimizing statistical analyses and ensuring study viability. Assuming a statistical power of 80% and a significance level of 5%, this sample size allows for the detection of statistically significant differences between the EOGIC and the non-EOGIC group in an exploratory approach. For continuous variables at a Cohen´s d of 0.385-medium size effect; and for categorical variables, with variables at a 10% prevalence in the non-EOGIC group, a15% of size-difference between groups; with variables at a 30–70% prevalence in the non-EOGIC group, a 20% difference between groups. Additionally, semi-supervised automatic learning will be employed for pan-tumor comparisons, a sample size of 60 EOGIC and 140 non-EOGIC patients is necessary to detect differences in an interest cluster of 20%.

This study is in agreement with international, national and local regulations for clinical studies (latest version of the Declaration of Helsinki, The Spanish Law for Biomedical Research and local regulations “Normas de Buena Práctica Clínica y Orden Foral 125/2009) as well as personal data protection (General Data Protection Regulation (RGPD-Regulation (EU) 2016/679), Spanish Organic Law 3/2018 and the local regulation “Resolution 1387–2017 of the Managing Director of the SNS-O”). Ethics Committee for Investigation with medicinal products from Navarra, have approved this project and a unified informed consent and patient-information sheet has been developed following guidelines of the Spanish Medication and Sanitary Product Agency (AEMPS). Previous to the inclusion, informed consent will be obtained for each patient.

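### With 1:2 allocation, the two tests named for continuous variables do not hold the 5% level for a difference in means if the EOGIC group is more variable; Welch's t-test would

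*Protocol article*

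**What the plan says.** The Statistical analyses section examines normality by histogram and by "the Shapiro–Wilk test, and homoscedasticity by Levene's test". It then states: "Group comparisons will be made using Student's t-test or Mann–Whitney U test for continuous variables". It names no unequal-variance test and does not say what happens when Levene's test rejects.

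The comparisons are run within each tumour type, "as well as at a pan-tumor level, comparing all EOGIC to non-EOGIC patients". Recruitment is fixed at unequal sizes, "following a ratio of 1 EOGIC: 2 non-EOGIC", and the planned numbers are "CRC-group A, 40 EOGIC and 80 non-EOGIC; GEC- group B, 20 EOGIC, 40 non-EOGIC; PC-group C, 20 EOGIC, 40 non-EOGIC". Summed, these give 80 EOGIC and 160 non-EOGIC patients, which matches "Two hundred and forty patients will be recruited". EOGIC is the smaller group in every comparison. The same section sends the same tests into the search for protein, microbiota and proteome signatures, followed by a false discovery rate correction.

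**The concern.** Student's t-test pools the two variances and weights the larger group more heavily. When the smaller group has the larger spread, the pooled standard error is too small and the test rejects too often. When the smaller group has the smaller spread, the test rejects too rarely. Unequal group sizes make this matter, and here they are built into the design.

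Mann–Whitney does not repair it. As a test of location, it also loses its level when spreads differ.

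So the plan checks for unequal variances but names no test that is valid for means when it finds them. At stake is whether the nominal 5% is the real rate, and whether the p-values passed to the FDR procedure mean what that procedure assumes.

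**Working it through.** **Inputs.** Group sizes 20/40, 40/80 and 80/160, and a 5% level, are from the article. Two-sided testing is assumed, as sidedness is not stated. The EOGIC/comparator SD ratio r is also an assumption, taken over 0.67 to 2, because the documents give no SDs.

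**The plan's own figure.** The sample-size paragraph after Figure 1 states "For continuous variables at a Cohen´s d of 0.385-medium size effect" at 80% power. By the normal approximation, d = (1.960 + 0.842) × √(1/80 + 1/160) = 2.802 × 0.1369 = 0.384. The noncentral t gives 0.3852, and power of 0.7996 at d = 0.385. The figure is reproduced and this point does not affect it.

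**Large-sample level of Student's t at 1:2.** Let the comparator SD be 1 and scale by the EOGIC group size.
- Variance that the test assumes: [(r² + 2)/3] × (1 + 1/2) = (r² + 2)/2
- True variance: r² + 1/2
- Actual level: 2 × [1 − Φ(1.96 × √(assumed/true))]

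| r | assumed | true | 1.96 × √(assumed/true) | actual level |
|---|---|---|---|---|
| 0.67 | 1.224 | 0.949 | 2.226 | 2.6% |
| 1 | 1.500 | 1.500 | 1.960 | 5.0% |
| 1.25 | 1.781 | 2.063 | 1.821 | 6.9% |
| 1.5 | 2.125 | 2.750 | 1.723 | 8.5% |
| 2 | 3.000 | 4.500 | 1.600 | 11.0% |

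**Simulation at the planned sizes.** Normal data, equal means, 10,000 samples per cell (about ±0.4 points at a 5% rate). The two-stage rule is an inferred reading: Student's t if Shapiro–Wilk and Levene both pass, otherwise Mann–Whitney. The last three columns give the range over the three sizes.

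| r | two-stage 20/40 | 40/80 | 80/160 | Student's t alone | Mann–Whitney alone | Welch |
|---|---|---|---|---|---|---|
| 0.67 | 2.9% | 3.5% | 4.1% | 2.3–3.1% | 3.2–4.1% | 4.5–5.4% |
| 1 | 5.1% | 5.0% | 5.0% | 4.9–5.0% | 4.8–5.0% | 5.0–5.1% |
| 1.25 | 6.6% | 5.8% | 6.2% | 6.4–6.8% | 5.3–6.0% | 4.6–5.2% |
| 1.5 | 7.5% | 6.9% | 6.4% | 8.1–8.5% | 6.4–6.8% | 4.6–5.0% |
| 2 | 8.4% | 8.5% | 8.5% | 10.5–11.2% | 8.3–8.5% | 4.7–5.1% |

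A repeat of the two-stage rule with 20,000 samples per cell gave 6.1–6.2%, 7.1–7.7% and 8.6–8.7% at ratios 1.25, 1.5 and 2. Allowing for simulation error, the rates are about 6–7%, 7–8% and 8.5–9%.

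**Is the pre-testing to blame?** No. At equal SDs the two-stage rule stays at 5.0–5.1%. At ratios 1.5 and 2 it inflates less than Student's t alone. Levene's test is only a partial safeguard: at 20/40 it detects a ratio of 1.5 in 49% of samples (97% at 80/160), and when it does detect it, the only other named test is Mann–Whitney.

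**Tail behaviour.** FDR procedures rely on small p-values. Put 3.481 (nominal 0.05%) in place of 1.96 at r = 1.5: 3.481 × √(2.125/2.75) = 3.481 × 0.879 = 3.060, an actual level of 0.22%. For Student's t, the inflation is about 4.4-fold there, against 1.7-fold at 5%.

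**The case against.** **The premise is not in the documents.** No SD is reported, so nothing shows that EOGIC is the more variable group. This stands, and the conclusion is conditional for that reason. A reader might infer unequal spread from the age bands of 18–50 and 60–75, but that concerns the spread of age, not of the measured variables. With uniform ages the variances are 32²/12 = 85.3 and 15²/12 = 18.75. Assume a common linear age effect and equal residual variance. If age explains 10% of the EOGIC variance, the comparator variance is 0.90 + 0.10 × 18.75/85.3 = 0.922 of it, an SD ratio of 1.04. A ratio of 1.5 would need age to explain about 71%. The age bands do not support ratios of 1.5 to 2.

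**The selection rule is inferred.** This also stands. A condensed article may leave the consequence of a Levene rejection to the full plan. If a rejection led to Welch's test, rates at ratios 1.25 to 2 would be 4.9–5.6% (80/160), 5.6–5.8% (40/80) and 6.1–6.7% (20/40). But the article names its tests, and Welch's is not one of them.

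**Skewed data might seem to make matters much worse.** Simulations with equal means, unequal SDs and skewed data do give higher rejection rates that rise with sample size. They are not clean false-positive rates: the two distributions then truly differ in the respect that Mann–Whitney tests, so part of what is counted is power. No figure for skewed data is relied on here.

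**The study is exploratory and its findings need validation.** True, and this limits the severity. The article nevertheless states a 5% level and plans FDR correction.

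**Conclusion.** The point holds in a conditional and modest form. The article names two tests for continuous variables, and under its own 1:2 allocation neither keeps the 5% level for a difference in means when spreads differ. On normal data, with the inferred two-stage rule, the false-positive rate is about 6–7%, 7–8% and 8.5–9% at SD ratios of 1.25, 1.5 and 2. With Student's t alone it is about 11% at ratio 2. At equal SDs there is no problem. If EOGIC is the less variable group (ratio 0.67), the rule is conservative at about 3–4%, and the cost is power.

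A reader might infer that the stated 5% level and the FDR control are wrong throughout, or that pre-testing causes the error. The documents support neither. The first depends on SDs they do not give, and the second is contradicted by the equal-SD results. Severity is minor. The change is still worth making, because a better test is available at almost no cost and the same p-values feed the signature analyses.

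**What to change.** In the Statistical analyses section, make Welch's unequal-variance t-test the default for comparing means of continuous variables between EOGIC and non-EOGIC patients, and drop Levene's test as a step in choosing the test. Where Mann–Whitney is used, state that it compares distributions, not means.

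The cost is a sentence or two of text. When variances are equal, Welch's test loses under one percentage point of power: 79.3% against 80.0% at 20/40, and 79.6% against 79.8% at 80/160. The planned sample size need not change.
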